### Blinding

The study employs a blinded evaluation method, with an uninformed third party doing the efficacy assessments regarding the group allocation. During the data summary phase, a blinded statistical analysis will be conducted, implementing the principle of separation among researchers, operators, and statisticians.

### Intervention procedures

All participants with chronic tinnitus will receive acupuncture treatment for a total of 10 times (Acupuncture treatment is given once every 2–3 days, and it takes about 28 days for 10 treatments). We chose 10 acupuncture times based on our previous research and clinical experience of acupuncture in the treatment of tinnitus (28, 29). We believe that the methods are representative and can effectively evaluate the efficacy of acupuncture in the treatment of tinnitus. After the completion of 10 acupuncture times, we will follow up the patients within 3 months in order to more comprehensively evaluate the efficacy of acupuncture. In this context, patients in the acupuncture group should ensure the occurrence of “de qi” (a sensation of numbness, tingling, and heaviness that arises after the acupuncture needle is inserted into the body (30)) after needling the acupoints. We use CT positioning. The therapeutic group has a puncture depth of about 20–25 mm, with the needle tip reaching the temporomandibular joint (see Figure 4). Needling techniques are applied to generate “de qi” and produce a therapeutic effect. While patients in the sham acupuncture group are not required to achieve “de qi.” The acupuncture depth of the placebo group is about 5-8 mm, and the needle will not reach the treatment depth. Acupuncture techniques will not be used, and “de qi” will be not produced. What is more, in sham acupuncture, we use precise needle insertion positions and applied force to avoid interference with the actual therapeutic effect on patients. Acupuncture depth only produces therapeutic effects when it reaches a certain depth, as shown in Figure 4 (31).

**Figure 4 fig4:**
[figure not shown]
Diagram of acupuncture depth.

### Acupuncture group

Acupuncture points prescription: The points to be used include Yifeng (affected side), Tinggong (affected side), Tinghui (affected side), Wai Guan (both sides), Zhongzhu (both sides), and Hegu (both sides) and so on. The participants in this study are licensed acupuncturists possessing more than 10 years of medical expertise of acupuncture. To guarantee strict compliance with the usual procedure for acupuncture, all professionals will undergo specific instruction on the acupuncture practices prior to the study. They will receive a booklet detailing the standardized procedures. Each acupoint will be located according to the WHO standards (32). For specific location, see Table 1.

**Table 1 tab1:** Locations of the selected acupoints.

Acupoints	Location
Yifeng (TE17)	Behind the earlobe, between the mastoid process and the mandible.
Tinggong (SI19)	In front of the tragus, when the mouth is open, at the depression.
Tinghui (GB2)	In front of the intertragic notch, at the posterior border of the condyloid process of the mandible.
Zhongzhu (TE3)	On the dorsum of the hand, between the 4th and 5th metacarpal bones, in the depression proximal to the MCP joint of the 5th digit.
Waiguan (TE5)	2 cun above the transverse crease of the wrist, between the ulna and radius bones.
Taixi (KI3)	In the depression between the medial malleolus and the Achilles tendon.
Xiawan (CV10)	2 inches above the navel, on the anterior midline.
Zhongwan (CV12)	4 inches above the navel, on the anterior midline.
Guanyuan (CV4)	3 inches below the navel, above the anterior midline.
Qihai (CV6)	1.5 inches below the navel, above the anterior midline.
Shangqu (KI17)	2 inches above the navel, with a 0.5 inch opening next to the midline.
Yindu (KI19)	4 inches above the navel, with a 0.5 inch opening next to the midline.
Hegu (LI4)	At the midpoint of the radial side of the second metacarpal bone.

Acupuncture procedure: Patients are placed in a supine position. After routine disinfection of the local skin around the ear, acupuncture needles with 40 mm in length and 0.25 mm in diameter (Hwato Brand, Suzhou Medical Instrument, China) are used for the three ear-adjacent points. Tinggong and Tinghui are punctured perpendicularly to the skin with a depth of approximately 20-25 mm. For “Yifeng point,” the needle is inserted with a slight forward tilt, meaning the direction of the puncture is toward the ear canal. The needle is inserted slowly with a depth of about 20-25 mm. The “De qi “is performed, which involves a small amplitude, low-frequency twisting manipulation with an amplitude of 180° and a frequency of less than 60 times per minute, until the patient feels a distinct sourness, numbness, and swelling in the ear that transmits into the ear canal. For the points on the limbs, acupuncture needles with 40 mm in length and 0.25 mm in diameter are used for conventional needling, and the technique of lifting, thrusting, and twirling with even tonification and reduction is applied. The Chinese Modified Massachusetts General Hospital acupuncture Sensation Scale (C-MASS) is used for quantification. All needles are retained for 30 min.

#### Sham acupuncture group

Acupuncture points prescription: In the selection of acupoint, the sham acupuncture group is the same as the acupuncture group.

Acupuncture operation: The patient is placed in a supine position, and after routine disinfection of the skin around the ears, the acupoints are punctured with 40 mm in length and 0.25 mm in diameter needle for superficial skin penetration (5–8 mm deep). The needle only needs to be inserted into the acupoints, without the need for “De qi “, and the needles are left for 30 min.

### Concurrent intervention and care

During the time frame for studying, Subjects are instructed to avoid engaging in any additional interventions which may influence the study outcomes, including, but not restricted to, medicine and behavioral treatment. If participants undergo other combined interventions for tinnitus, researchers must document pertinent facts for future examination. Nevertheless, for participants with comorbidities include hypertension, diabetes, and various other chronic conditions, they may persist with their standard medication and therapies. Researchers will document the identities of these comorbidities, drugs, and therapy in the case type of report.

### The process of fNIRS gage and record analysis

Our experiment’s FNIRS gage apparatus, the ETG-4000 (Hitachi Ltd., Japan), uses two wavelengths of near-infrared light (695 and 830 nm) to find differences in oxygenated hemoglobin (HbO), deoxygenated hemoglobin (HbR), and total hemoglobin (HbT). Hemoglobin variations may be monitored 2–3 cm below the surface, which corresponds to the brain’s cortex, using 3 cm between the source and the detector. The measurements will be conducted using a 52-channel fNIRS device. This system includes 33 probes (17 emitters and 16 detectors) arranged in a 3 × 11 configuration fixed to the scalp, in accordance with the international 10–20 system (33). Measurement channels are established between each emitter-detector pair, producing a total of 52 channels. See Figure 5 for the channels. The fNIRS probes will include the frontal skin and superior temporal skin. Upon stabilization of the probes, the signal power of every channel. Will be assessed. Signals from channels may be influenced by the cleanliness of the probes and obstructions, like as pile, between the probes and the scalp. Consequently, if the signal intensity of a channel is determined to be inadequate, prompt actions like scalp cleansing, probe adjustment, and hair repositioning will be implemented.

**Figure 5 fig5:**
[figure not shown]
Based on the worldwide 10–20 system, Figure 2 shows the channel configuration of fNIRS. It has 52 channels (numbers), 16 detectors (blue squares), and 17 light emitters (red squares).

Data from the ETG-4000 will be loaded into NIRS-KIT software as CSV files, a MATLAB-based software that provides researchers with an open instrument for analyzing fNIRS about data within a single suite (34). The fNIRS data will undergo preprocessing, including detrending, motion correlation, and filtering to eliminate hindrance about external variables. After preprocessing, the data will be eligible for calculating the strength of functional connectivity between regions. For specific measurement results, see Figure 6.

**Figure 6 fig6:**
[figure not shown]
fNIRS brain functional connectivity.

### ABR scanning

Auditory brainstem response (ABR) measurements will be conducted using the Danish Interacoustics Eclipse, EP25 auditory evoked potential instrument on subjects. The testing will be performed in a sound (electric) shielded chamber with an environmental noise level of ≤30 dB. The ground electrode will be placed between the eyebrows, the recording electrode on the center of the forehead, and the reference electrodes on both mastoids with a resistance of less than 5kΩ. The stimulating sound will be a click, with stimulation frequencies of 11.1 times/s and 51.1 times/s, a total of 1,024 superimpositions, and a recording time of 10 s. For specific measurement examples, see Figure 7.

**Figure 7 fig7:**
[figure not shown]
ABR report.

### Outcome measures

Clinical Results: Clinical result metrics encompass the Tinnitus Handicap Inventory (THI), ABR testing, and fNIRS data collection. Evaluations will be carried out at baseline, after 10 treatment sessions.

THI score: The THI is a self-reported checklist that’s quick, simple. To manage and interpret, and covers a wide range of issues. It consists of 25 items, each scored from 0 to 4. An elevated THI indicates a more severe level of tinnitus.

ABR testing: The test records the peak latencies (PL), wave amplitudes, and interpeak intervals (IPL) of the subjects at various stimulation rates, as well as the differences in PL and IPL at the two stimulation rates (ΔPL and ΔIPL) to evaluate the function of the peripheral auditory nerve.

fNIRS data acquisition and processing: Cortical blood oxygen data will be collected to evaluate the central function of the subjects.

fNIRS results: fNIRS scans will be conducted at baseline, and after 10 treatment sessions. The blood oxygen concentrations measured include the concentrations of oxygenated hemoglobin (HbO), hemoglobin that has lost oxygen (HHb), and total hemoglobin (THb) in every measured channel.

fNIRS functional connectivity intensity: The intensity of functional connectivity between regions can quantify the relationships between routes or areas of interest within the fNIRS time plots. This is computed using the Pearson correlation coefficient between the average time series of any pair of channels of interest. The functional connectivity strength between channels of interest, as well as between channels of interest and other channels, is computed using NIRSKIT software. This software will help in analyzing the correlation between the time series data from different channels, providing insights into the connectivity patterns within the brain that may be associated with tinnitus and its treatment.

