### Analytical statistics

Date analysis will be done using SPSS version 26 (IBM Corporation, Armonk, NY, 2019), with a two-sided significance threshold established at 0.05. In terms of data description, continuous data is presented as mean ± standard deviation (x ± s), and categorical and ordinal data is stated as proportions (%). The intervention effects will be represented by OR and 95% CI. Data on immediate and cumulative effects of the two acupuncture groups, clinical scoring, ABR parameter analysis, and fNIRS data analysis is compared using T-tests. Permutation tests will be used, and multiple comparisons will be examined using False Discovery Rate (FDR) correction. The differences in THI scores, ABR parameters, and functional values of brain regions will be analyzed for correlation using Pearson’s correlation analysis, with inspection level *α* = 0.05.

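### No outcome is named primary among THI, ABR and fNIRS, the sample size is tied to none of them, and it is not stated whether the FDR correction covers the correlations tested at 0.05

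*Protocol article*

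**What the plan says.** **Outcomes.** The Outcome measures section of the protocol article states: "Clinical result metrics encompass the Tinnitus Handicap Inventory (THI), ABR testing, and fNIRS data collection". The article's text calls no outcome primary or secondary. That section gives assessments at baseline and after 10 sessions. Intervention procedures adds a follow-up within 3 months, also meant to evaluate efficacy.

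**Sample size.** Sample size estimation uses a formula for two rates, P1 and P2. It gives no values for them and names no binary outcome. It arrives at 30 per group, then 36 per group and 72 in total.

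**Analysis.** Analytical statistics contains these elements:
- an overall level, "with a two-sided significance threshold established at 0.05";
- one test for every domain: "clinical scoring, ABR parameter analysis, and fNIRS data analysis is compared using T-tests";
- an effect measure: "The intervention effects will be represented by OR and 95% CI";
- multiplicity: "Permutation tests will be used, and multiple comparisons will be examined using False Discovery Rate (FDR) correction", with no family and no FDR level;
- then, in the next sentence: "The differences in THI scores, ABR parameters, and functional values of brain regions will be analyzed for correlation using Pearson’s correlation analysis", at a level of 0.05 and with no mention of FDR.

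**The concern.** A primary outcome fixes which result carries the efficacy claim and at what error rate. Here a reader cannot recover it from the rest of the article. The sample size points to a rate, the effect measure to a binary outcome, and the test to a continuous one. The listed outcomes are a score, electrophysiological measures and haemoglobin or connectivity values. Once the data are in, any of the three domains could be presented as the efficacy result.

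The undefined FDR family adds to this. Whether THI is tested alone or pooled with the imaging tests changes the threshold it has to meet. The correlations are meant to link the clinical, target-organ and central levels, which is the mechanistic core of the trial. They cross several ABR measures with several brain values at a level of 0.05 that may or may not be adjusted.

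**Working it through.** **1. The plan's own figure.** Read as a difference of arcsines in degrees, the formula is n = 1641.4 × [(u_α + u_β) / (arcsin√P1 − arcsin√P2)]², with α = 0.05 and β = 0.20. Without P1 and P2, the 30 per group can be neither reproduced nor refuted. More than one pair reaches it: 0.90 against 0.60 gives 29.8 two-sided, and 0.80 against 0.50 gives 29.9 one-sided. The step to 36 is 30 × 1.2. Nothing here identifies an outcome.

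**2. How many group contrasts there are.**
- THI: 1.
- fNIRS: "producing a total of 52 channels", each with three haemoglobin signals, so 52 × 3 = 156.
- ABR (assumption: waves I, III and V, three intervals, one ear): 6 latencies + 6 amplitudes + 6 intervals over two rates, plus 3 + 3 rate differences = 24. Two ears would give 48.
- Total with one ear: 1 + 24 + 156 = 181, before connectivity.

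Connectivity depends on the number k of channels of interest, which is not stated. Pairs per signal are k(k−1)/2 + k(52−k): 51 for k = 1, 291 for k = 6, and 1,326 only if all 52 channels are of interest.

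**3. Chance of at least one positive group contrast when nothing works.** If three independent domains are each held at 5%, this is 1 − 0.95³ = 0.143. A simulation of 10,000 runs used Benjamini-Hochberg at 5% and equal correlation within the ABR and fNIRS families, with the domains independent of one another:

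| Correlation within family | 0 | 0.3 | 0.5 | 0.8 |
|---|---|---|---|---|
| THI at 0.05, FDR within ABR and within fNIRS, any counts | 14.5% | 13.8% | 11.9% | 8.8% |
| FDR over one pooled family of 181 | 5.1% | 4.7% | 3.5% | 1.8% |
| No correction at all | over 99.9% | 99.3% | 93.2% | 56.8% |

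One named primary tested once gives 5%.

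**4. What the family means for THI.** Tested alone, THI needs p ≤ 0.05. In a pooled family of 181 where no other test is rejected, it needs p ≤ 0.05/181 = 0.00028. The article allows either.

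**5. Correlations, if FDR does not cover them.**
- With 24 ABR measures and 6 regional values (both assumed): 24 THI–ABR + 6 THI–fNIRS + 24 × 6 = 144 ABR–fNIRS, so 174 tests. Expected false positives under the null: 174 × 0.05 = 8.7. If the tests were independent, at least one would be near certain (1 − 0.95¹⁷⁴ > 0.999).
- Upper range, with all 156 channel signals in place of regional values: 24 + 156 + 24 × 156 = 3,924 tests, and 3,924 × 0.05 = 196 expected.

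**The case against.** **FDR is in the plan.** With it, a chance finding on the group contrasts is not likely: about 2% to 5% with one family and 9% to 14% with three. A reader might infer that a positive trial is probable by chance alone. The documents do not support that, because such rates arise only if the stated correction is ignored. The article also never says that success in any one domain counts as success. This stands. The 9% to 14% describes what the plan leaves open, not a rule it adopts.

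**The correlations may be covered.** The FDR sentence comes immediately before, its scope is not restricted, and the repeated 0.05 is compatible with FDR at that level. This also stands. The text is ambiguous, and calling the correlations uncorrected is an inference.

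**The large counts are upper limits.** A reader might speak of thousands of fNIRS tests, but the number of channels of interest is not given. The correlation sentence refers to brain regions, so 174 is closer to the text than 3,924. Nor can one say that most significant correlations would be noise: an expected count under the null does not give the share of significant results that are false.

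**T-tests and permutation tests are compatible**, since a permutation can supply the p-value of a t statistic. Naming both is no contradiction.

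**Detail belongs in the SAP or the full protocol.** That is fair for the exact FDR families. It does not reach the primary outcome, which is core protocol content in an article that claims to follow SPIRIT. Nor is this mere silence: the article sizes the trial on rates that none of its three outcomes measures.

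**Conclusion.** The point holds and should be fixed before analysis, chiefly because of the missing primary outcome. As written, no single result can confirm or refute efficacy at a known error rate, and the sample size supports none of the listed outcomes.

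The size is moderate for the group comparisons: about 9% to 14% against 5% if any of three domains may carry the claim. This assumes 24 ABR measures, 156 channel signals and domains independent of one another. Positive dependence between domains would lower it.

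For the correlations the size depends on an unresolved reading. If FDR does not apply, about 9 false positives are expected under the null with 174 tests, and up to about 196 at the extreme count. If FDR does apply, this part reduces to a clarification.

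This assessment rests on the article's text; the schedule in Figure 1 could not be checked. If it marks a primary outcome, the text and the sample size still need to agree with it.

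**What to change.** 1. **Name one primary outcome and one time point**, tested once at two-sided 0.05 outside any FDR family. The between-group THI difference after 10 sessions fits the hypothesis of tinnitus relief in the Discussion. The second purpose in the Abstract is auditory function, however, so the choice is the sponsor's.
2. **Restate the sample-size basis for that outcome.** If it is binary, define it and give P1 and P2. If it is a mean difference, give the difference and the standard deviation. As orientation, 30 per group at 80% power and two-sided 0.05 detects √(2/30) × (1.960 + 0.842) = 0.72 SD by the normal approximation. Align the effect measure with the outcome.
3. **Make the other domains secondary**, with Benjamini-Hochberg FDR at 5% within each modality.
4. **Settle the correlations.** Either place them inside a stated FDR family, or report them as exploratory estimates with confidence intervals and no significance claim.

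**Cost.** No new data are needed. Fewer mechanistic results will be called significant, and restating the sample size may show that 72 patients suffice only for a fairly large effect on the chosen outcome.

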Given the significant potential of fNIRS and ABR in tinnitus research, and the constraints of prior studies, we have developed this randomized controlled experiment (RCT) to investigate the pathological mechanisms of chronic tinnitus using fNIRS and ABR. The objectives of this trial are: (1) To compare the auditory brainstem response parameters and extracerebral oxygen levels of the cerebral cortex between chronic tinnitus patients and healthy subjects, and to compare the correlation of peripheral-central auditory function under different physiological states. (2) To compare the intervention effects of acupuncture versus sham acupuncture on chronic tinnitus patients from clinical manifestations, ABR parameters, and extracerebral oxygen levels of the cerebral cortex, exploring the correlation of acupuncture intervention on chronic tinnitus from the peripheral-central auditory function at three levels: clinical, target organ, and central.

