#### Preprocessing

Bandpass filtering is applied to the signals to remove high-frequency interference. A combination of empirical mode decomposition and wavelet transform is used to filter out baseline drift and physiological interference in the signals. A correlation-based signal improvement algorithm is employed to remove motion interference from the signals. Data is segmented according to the position of the target stimulus.

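### The fNIRS outcome is worded as cortical oxygen level and per-channel concentration, but the described measurement and preprocessing leave only within-recording variation, so the t-tests cannot support a conclusion about level

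*Protocol article*

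**What the plan says.** **What is to be compared.** The first objective at the end of the Introduction is "To compare the auditory brainstem response parameters and extracerebral oxygen levels of the cerebral cortex between chronic tinnitus patients and healthy subjects". The second compares acupuncture with sham "from clinical manifestations, ABR parameters, and extracerebral oxygen levels of the cerebral cortex". Study design repeats the patient-versus-healthy comparison. Outcome measures schedules fNIRS scans at baseline and after the ten sessions and defines the result for each channel: "The blood oxygen concentrations measured include the concentrations of oxygenated hemoglobin (HbO), hemoglobin that has lost oxygen (HHb", followed by total haemoglobin. Analytical statistics assigns t-tests to the fNIRS data.

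**What is measured.** The section on fNIRS measurement says that the two-wavelength device is used "to find differences in oxygenated hemoglobin (HbO), deoxygenated hemoglobin (HbR), and total hemoglobin (HbT", and adds: "Hemoglobin variations may be monitored 2–3 cm below the surface".

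**What is done to the signal.** The text after Figure 5 says: "The fNIRS data will undergo preprocessing, including detrending, motion correlation, and filtering". The Preprocessing subsection applies a band-pass filter, then a decomposition and wavelet step to "filter out baseline drift and physiological interference in the signals". It then cuts the data into segments around a target stimulus.

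**The concern.** The outcome is worded as a quantity of haemoglobin that one person has more or less of than another, or more or less of after treatment than before. The measurement section speaks only of differences and variations, and the preprocessing is of a kind that discards a recording's constant component. If the constant is gone, a comparison of processed signals between people, arms or visits carries no information about level.

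The risk lies in interpretation. A null t-test could be reported as showing that patients and healthy subjects have the same cortical oxygen level, or that acupuncture does not change it. A positive one could be reported as acupuncture having raised cortical oxygen. Neither statement would follow from the data as processed, although oxygen level is named in both objectives.

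**Working it through.** The plan gives no figure that depends on this point, so there is none to reproduce. The check compares the stated outcome with the stated measurement and follows a constant level through the stated processing.

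**Inputs from the article**
- Outcome: concentrations of three haemoglobin signals per channel (Outcome measures).
- Channels: 52 (fNIRS measurement section). Level readouts per scan: 52 × 3 = 156.
- Comparisons: 72 patients with 15 healthy subjects, 36 with 36 between arms, and the baseline scan with the scan after ten sessions.
- Processing: detrending, band-pass filtering and removal of baseline drift (text after Figure 5, and Preprocessing).

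**Step 1: the instrument text.** It mentions differences and variations. Nowhere does the article describe an absolute concentration, a calibration, or a zero shared by different people or visits. This leaves a level outcome without support, but it does not by itself prove that the device cannot give one.

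**Step 2: the processing.** Write one channel of one recording as

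y(t) = L + x(t),

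where L is the constant level and x(t) is the variation around it.
- *Linear detrending* subtracts a fitted intercept and slope. The residuals sum to zero, so the processed mean is 0 whatever L was.
- *Band-pass filtering.* If the detrending removed only the slope and kept the intercept, L would still be there. A filter whose pass band starts above zero frequency has zero gain for a constant, so L is removed here. The article does not give the band. I assume only that a band-pass filter has a lower cut-off above zero.
- *Baseline-drift removal* acts on the slowest component of the signal, where a constant also sits.

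**Step 3: the comparison.** For two people, or two visits, with levels L₁ and L₂, the processed signals are functions of x₁(t) and x₂(t) alone. The difference L₁ − L₂ does not enter the t-test. A larger sample does not bring it back.

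**Step 4: what survives**
- *Functional connectivity* is a Pearson correlation between channel time series. For constants a and b, r(y₁ + a, y₂ + b) = r(y₁, y₂). In a numerical check with offsets of 5 and 50 added to two correlated series, r was 0.713 before and after.
- *Slope* is unaffected by a constant, because the derivative of L + x(t) is that of x(t). It should be fitted over a segment, since linear detrending sets the slope over the whole detrended record to zero.
- *Approximate entropy* depends on distances between values within the series, from which L cancels.
- *Change from a reference interval* is the segment mean minus the mean of a pre-stimulus interval. L cancels here too, and the result is interpretable if a stimulus or task separates the two intervals.

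Of the features listed under fNIRS signal feature extraction and modeling, only the mean value is exposed to the problem, and only when it is read as a level.

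**The case against.** **Concentration may be shorthand for concentration change.** The target stimulus under Preprocessing, and the channel selection by amplitude change during acquisition, both point that way. This is a fair reading of what may have been intended. But the objectives, Study design and Outcome measures all say level or concentration, and no fNIRS stimulus, task, rest period or reference window is described from which a change would be taken. If change was meant, the wording still needs correcting.

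**The article does not specify a t-test on mean concentration in each channel.** True: it says only that fNIRS data are compared by t-test. The point is therefore limited to what such tests can support when applied to the outcome as defined.

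**An article condenses.** The reference window and the exact summary measure may be in a fuller document, and their absence is not counted as a fault here. What remains is a mismatch between an outcome and a processing chain that are both stated in the text.

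**Stronger readings that the article does not support**
- A reader might infer that the device records only change from each recording's own zero, so that the limit holds whatever the preprocessing. The article says neither *only* nor anything about a zero, and in its loose wording *differences* could mean differences between people or conditions. The firmer ground is the detrending, filtering and drift removal.
- A reader might want the loss of power quantified by simulation. A simulation that gives each person an offset, subtracts it and then fails to find it only restates its own assumption, so no rejection rates are offered.
- A reader might conclude that the fNIRS component as a whole fails. It does not, because connectivity and the other within-recording features remain usable.

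**Conclusion.** The concern holds in limited form. The stated outcome is a level, no absolute or calibrated concentration is described, and the stated preprocessing removes any constant level before testing. T-tests on the processed signal cannot support a conclusion about cortical oxygen level between patients and healthy subjects, between arms or across visits.

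Its reach is the 156 channel-by-signal level readouts per scan and the oxygen-level part of both objectives. The THI, the ABR parameters and functional connectivity are untouched, as are slope and entropy features.

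The conclusion rests on two assumptions: that preprocessing is applied to the data behind the concentration outcome, as the article says of the fNIRS data generally, and that detrending and band-pass filtering have their usual meaning. If concentrations were instead taken from unprocessed exports, the case would rest on the instrument description alone and would be weaker, though the article would still offer no basis for a common scale across people and visits.

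**What to change.** In the objectives (Introduction), Study design and Outcome measures, replace the wording on levels and concentrations with within-recording quantities.
- **Functional connectivity**, as already defined under Outcome measures.
- **If the target stimulus under Preprocessing is a real fNIRS stimulus or task:** describe it, and define the outcome as the change in each haemoglobin signal from a stated pre-stimulus reference interval in the same recording.
- **If there is no such stimulus:** rely on connectivity and other within-recording features, such as segment slope and approximate entropy, and do not use a change score.

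Apply the between-group and between-visit tests only to these quantities. In either case, state that no conclusion will be drawn about absolute cortical oxygen level.

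The cost is small. Connectivity and the other features are already planned, so the change is one of wording. A change score can use the planned recordings only if they contain a usable reference interval, which the article does not show. The trial gives up any claim about oxygen level, which the described measurement could not support.
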